# Anaesthetist-controlled versus patient-maintained effect-site targeted propofol sedation during elective primary lower-limb arthroplasty performed under spinal anaesthesia (ACCEPTS): study protocol for a parallel-group randomised comparison trial

**DOI:** 10.1186/s13063-019-3228-4

**Published:** 2019-02-13

**Keywords:** Propofol sedation, Patient-maintained propofol sedation, Regional anaesthesia, Joint arthroplasty, Procedural sedation

## Abstract

**Background:**

The clinical efficacy of effect-site targeted patient-maintained propofol sedation (PMPS) compared to anaesthetist-controlled propofol sedation (ACPS) for patients undergoing awake joint replacement surgery is currently unknown. There is no commercially available medical device capable of delivering PMPS so we have designed and built such a device. We plan a clinical trial to compare PMPS to ACPS and to collect data relating to the safety of our prototype device in delivering sedation.

**Methods:**

The trial is an open-label, randomised, controlled superiority trial recruiting adults who are undergoing elective primary lower-limb arthroplasty with sedation by propofol infusion by effect-site targeting into two equal-sized parallel arms: PMPS and ACPS. The primary research objective is to compare the body-weight-normalised rate of propofol consumption when sedation for surgery on adults undergoing elective primary lower-limb arthroplasty under spinal anaesthesia is patient-maintained versus when it is anaesthetist-controlled. The study primary null hypothesis is that there is no difference in the rate of propofol consumption when sedation is patient-maintained versus anaesthetist-controlled.

**Discussion:**

This is the first trial to test the superiority of effect-site-targeted patient-maintained propofol sedation versus anaesthetist-controlled propofol sedation in terms of total propofol consumption during the sedation period. The results of this trial will help inform clinicians and device manufacturers of the clinical efficacy and safety of patient-maintained propofol sedation applied to a common operative setting.

**Trial registration:**

International Standard Randomised Controlled Trial Number Registry, ISRCTN29129799. Prospectively registered on 12 June 2018.

**Electronic supplementary material:**

The online version of this article (10.1186/s13063-019-3228-4) contains supplementary material, which is available to authorized users.

## Background

The most commonly performed lower limb surgical arthroplasty procedures in the UK are primary hip replacement and primary knee replacement; respectively, 93,234 and 102,519 replacements were performed in 2016 (excluding Scotland) [1]. Regional anaesthesia, consisting of a spinal anaesthetic with or without peripheral nerve blockade, provides excellent operating conditions and post-operative analgesia, reduces the risk of venous thromboembolism, reduces transfusion requirements in the peri-operative period and avoids some of the risks associated with general anaesthesia [2].

Some patients are willing to experience surgery awake, but a significant proportion of patients are fearful of this experience pre-operatively and experience varying degrees of anxiety before and during the operation [3, 4]. Anaesthetists commonly supplement spinal anaesthesia with sedation medication delivered intravenously for lower limb arthroplasty in anxious patients. The aim of sedation is to reduce anxiety and promote psychological comfort, while minimising the physiological side effects induced by deeper planes of sedation.

Sedation for lower limb arthroplasty is often provided by the supervising anaesthetist using propofol by intravenous computer-assisted target-controlled infusion (anaesthetist-controlled propofol sedation (ACPS)) [5]. A target-controlled infusion (TCI) device delivers a variable rate of propofol in order to obtain and maintain a specified effect-site (i.e. brain) drug concentration, until such time as a new concentration is set by the supervising anaesthetist. Their use is standard anaesthesia practice in the UK.

There is, however, an unpredictable individual dose response to drugs inducing sedation, even using modern ACPS with TCI systems. Furthermore, anaesthetists have been shown to be poor judges of the pre-operative anxiety states of individual patients [6]. For a variety of reasons, including anxiety itself, patients do not always have preconceived expectations about how sedated they wish to be for surgery and these expectations are not always clearly communicated to (or understood by) the treating anaesthetist.

For these reasons it is difficult for anaesthetists to sedate each individual to their preferred level using ACPS. Under-sedation results in an anxious patient because their anxiolytic requirements are unmet during surgery. Over-sedation results in a patient receiving an unnecessarily deep level of sedation and heightened exposure to the associated physiological harms even though the patient would have willingly experienced surgery at a lighter plane of sedation.

Patient-maintained propofol sedation (PMPS) involves the use of a TCI system delivering propofol where the effect-site concentration is influenced by the patient using a handheld trigger. Allowing patients to influence the depth of their sedation with a propofol TCI system has already been described in small case series in healthy volunteers [7] and in general [8], dental [9] and ambulatory outpatient surgery [10]. There are only three randomised controlled trials of PMPS and none of these use the Schnider effect-site-targeted propofol TCI model [5] to compare PMPS against ACPS [11–13]. Our aim is to assess the clinical efficacy of PMPS compared to ACPS. There is no commercially available device to perform PMPS, previous studies having relied on prototype devices. We have therefore designed and built a device capable of delivering PMPS for use in this clinical trial.

## Methods/design

A standard protocol items: recommendation for interventional trials (SPIRIT) checklist detailing the items addressed in this clinical trial protocol is provided as Additional file 1.

### Study objectives

The primary research objective is to compare the body-weight-normalised rate of propofol consumption when sedation for surgery on adults undergoing elective primary lower-limb arthroplasty under spinal anaesthesia (effect-site-targeted with propofol) is patient-maintained versus when it is anaesthetist-controlled. The primary outcome will be expressed as milligrams propofol per kilogram actual body weight per hour of the sedation period. The sedation period is defined as the time from commencement of the allocated sedation regimen by the supervising clinical anaesthetist (which will be after spinal blockade is confirmed by clinical dermatomal testing) until the sedation regimen is discontinued at the end of surgery (which will be at the application by the operating surgeon of clips to skin).

The study primary null hypothesis is that there is no difference in the rate of propofol consumption when sedation it is patient-maintained versus anaesthetist-controlled. The primary alternative hypothesis is that a patient-maintained propofol sedation regimen will result in a minimum 29% reduction in the rate at which propofol is consumed over the course of the sedation period compared to anaesthetist-controlled propofol sedation.

The secondary research objectives are:To establish whether patients are less deeply sedated intra-operatively during patient-maintained sedation compared to anaesthetist-controlled sedation.To assess whether patients undergoing PMPS have equal reductions in peri-operative anxiety compared to patients undergoing ACPS.To observe whether patients undergoing PMPS have comparable post-operative satisfaction with their sedation experience compared to patients undergoing ACPS.To explore whether patients who have undergone PMPS are fit for discharge from the post-anaesthetic care unit (PACU) sooner than patients who have undergone ACPS.To determine if patients undergoing PMPS have calculated effect-site concentrations of propofol that are lower than in patients who undergo ACPS.To examine how many times patients using PMPS press their trigger button to increment their dose (successful button press), how many times they press the button while the device is locked out (unsuccessful button press) and whether there is a relationship between pre-operative anxiety state and use of the trigger system.To determine whether patients undergoing PMPS experience a different incidence of airway, respiratory or cardiovascular sedation-related side-effects than patients who have undergone ACPS. Airway sedation-related side-effects include partial or complete airway obstruction that requires the usual clinical anaesthetist to apply one of the following interventions: chin-lift, jaw thrust, nasopharyngeal airway insertion, oropharyngeal airway insertion, laryngeal mask insertion or endotracheal tube insertion. Respiratory sedation-related side-effects are respiratory rate fewer than 8 breaths per minute or arterial oxygen saturations less than 88% in patients with chronic obstructive pulmonary disease (COPD) or 94% in all other patients. Cardiovascular sedation-related side-effects include heart rate or blood pressure reduction greater than 20% from baseline, but such events may be related to spinal anaesthesia rather than the sedation. All such events will be noted by a study investigator and reviewed to determine the likely aetiology. There are no objective clinical criteria to determine this, but routine clinical practice is to assimilate the presented information to estimate the likely contribution from sedation, spinal anaesthesia and/or another cause.To determine whether patients undergoing PMPS experience different health-related quality of life outcomes compared to patients undergoing ACPS.

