
### Study design and setting

The trial is an open-label, randomised, controlled superiority trial recruiting adults who are undergoing elective primary lower-limb arthroplasty with sedation by propofol infusion by effect-site targeting into two equal-sized parallel arms: PMPS and ACPS. The study will be run as a single-centre study at Nottingham University Hospitals National Health Service (NHS) Trust. The trial will be conducted only in a secondary care setting.

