### Statistical plan

All data collected will be summarised for reporting purposes using descriptive statistics. The hypothesis test associated with the primary outcome will compare the two mean consumption rates using standard statistical tests chosen appropriate to underlying assumptions (e.g. two-sample *t* test and the Wilcoxon-Mann-Whitney test). Testing will be performed using datasets formed according to inclusions based on intention to treat. *P* values will be reported, with values less than 5% declared statistically significant.

We will report analyses of secondary outcomes for complete cases that contain no major clinical investigation plan violations. Amongst these, button-press data will be modelled using count data regression methods, with extension to bivariate models to distinguish between successful presses and unsuccessful presses. The panel time-series of propofol consumption rates collected throughout the sedation period alongside button presses will together be modelled using marked-point process methods. Ordinal responses recorded on a Likert scale (peri-operative anxiety, patient satisfaction) will be compared across trial arms using parametric methods suitable to underlying assumptions and non-parametric methods, such as the Wilcoxon rank sum test. Preoperative and post-operative quality of recovery total scores will be compared using the Wilcoxon matched pairs test. Inter-item correlations will be computed and associations between scored items will be compared using Spearman rank correlation. The Bonferroni correction to allow for multiple comparisons will be applied. Qualitative data obtained from structured questions will be coded and computer-analysed. Any missing outcome data will be imputed using either a last-observation-carried-forward rule or, for the subset of comparable secondary outcomes, use data routinely measured and recorded as part of usual clinical care.

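### Equal anxiety reduction and comparable satisfaction are set as objectives, but the only analyses named are tests of difference, which cannot show sameness

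*Protocol article*

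**What the plan says.** Under Study objectives, the second secondary objective is "To assess whether patients undergoing PMPS have equal reductions in peri-operative anxiety compared to patients undergoing ACPS". The third is "To observe whether patients undergoing PMPS have comparable post-operative satisfaction with their sedation experience compared to patients undergoing ACPS". Most of the other between-arm objectives in the same list are worded as a direction or a difference, so these two stand apart. Under Study design and setting, the framework is given as follows: "The trial is an open-label, randomised, controlled superiority trial".

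The Statistical plan says how the two outcomes will be handled: "Ordinal responses recorded on a Likert scale (peri-operative anxiety, patient satisfaction) will be compared across trial arms using parametric methods" that suit the underlying assumptions, and "non-parametric methods, such as the Wilcoxon rank sum test". Values below 5% are to be declared significant. Later in the same paragraph, directly after the sentence on inter-item and Spearman correlations, comes "The Bonferroni correction to allow for multiple comparisons will be applied". Neither the number of comparisons nor the outcomes covered are given. Secondary analyses use complete cases without major violations.

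The article states no margin for either outcome and no confidence-interval criterion for calling the arms equal or comparable. The Sample size calculation rests on the propofol rate alone.

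**The concern.** A t test or a Wilcoxon rank sum test takes no difference as its null hypothesis. It can give evidence against sameness, but failing to reject the null is not evidence for it, least of all in a trial sized for another outcome. With these objectives and these tests, the only result that could seem to answer an equality question in the affirmative is a non-significant p value. That result becomes more likely as the sample gets smaller or the threshold stricter.

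At stake is what the trial can say about anxiety and satisfaction beside its propofol result. A report could state that propofol use fell and anxiety relief was equal when the data were compatible with a material deficit.

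**Working it through.** **Inputs from the article.** Mean propofol rates are 1.580 (SD 0.755) and 2.231 (SD 0.915). The test is Welch's t test with two-sided 5% significance and 90% power. The required number is 72, raised to 80 for 10% drop-out, in two equal arms. That gives 36 to 40 per arm.

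**Assumptions.** The article gives no SD, effect size or margin for anxiety or satisfaction, and no number of comparisons. Effects are therefore in SD units, with a true deficit of 0.5 SD for illustration and 5 to 10 comparisons for Bonferroni. The t test stands in for the Wilcoxon test on ordinal data.

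**1. The plan's own figure.** The difference is 2.231 − 1.580 = 0.651. The root-mean-square SD is √((0.755² + 0.915²)/2) = 0.839, so the standardised effect is 0.651/0.839 = 0.776. Welch power from the noncentral t is 89.2% at 35 per arm and 90.1% at 36 per arm, hence 72; and 72/0.9 = 80. The stated sample size reproduces, for the primary outcome.

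**2. Power of a difference test for a 0.5 SD deficit.** With n per arm, df = 2n − 2 and noncentrality 0.5 × √(n/2), which is 2.121 at n = 36 and 2.236 at n = 40. Power is the probability that a noncentral t exceeds the critical value at 0.05/m, two-sided.

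| Comparisons m | Power, n = 36 | Missed | Power, n = 40 | Missed |
|---|---|---|---|---|
| 1 (no correction) | 55% | 45% | 60% | 40% |
| 5 | 31% | 69% | 35% | 65% |
| 10 | 23% | 77% | 27% | 73% |

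**3. Largest observed gap that stays non-significant.** This is the critical t × √(2/n).
- Without correction: 1.994 × 0.2357 = 0.47 SD at n = 36, and 1.991 × 0.2236 = 0.45 SD at n = 40. These are also the half-widths of the 95% confidence interval.
- With m = 5: 2.648 × 0.2357 = 0.62 SD at n = 36.
- With m = 10: 2.899 × 0.2357 = 0.68 SD at n = 36.

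Bonferroni therefore widens the range of observed differences that would come out non-significant.

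**4. What a margin-based claim could achieve.** For non-inferiority at one-sided 2.5% with a true difference of zero, power is Φ(margin/√(2/n) − 1.96). For a 0.5 SD margin at n = 36 this is Φ(0.5/0.2357 − 1.96) = Φ(0.161) = 56%.

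| Margin (SD) | Power, n = 36 | Power, n = 40 | n per arm for 80% power |
|---|---|---|---|
| 0.3 | 25% | 27% | 175 |
| 0.4 | 40% | 43% | 99 |
| 0.5 | 56% | 61% | 63 |
| 0.8 | 92% | 95% | 25 |

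Two-sided equivalence (two one-sided tests at 5%) is harder: 37% and 45% power at 0.5 SD for n = 36 and n = 40.

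**The case against.** The best defence is that the objectives are open questions, to assess or to observe whether something is so, and that a difference test can answer them in the negative. Satisfaction in particular is a descriptive aim, and all data are to be summarised descriptively. The article is condensed, and margins, intervals and multiplicity scope are commonly left to an analysis plan. Low power on secondary outcomes is also ordinary in a trial sized on its primary outcome.

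Much of this stands, and it keeps the point modest. What remains is that the article does not leave the method open. It names the objective, the kind of test and the decision rule, and that test cannot support an affirmative answer.

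Several stronger readings are tempting but not supported:
- **That the trial will read non-significance as equality.** No sentence says so. It is an inference from the pairing of objective and test.
- **That Bonferroni certainly covers these outcomes.** The sentence follows the correlation analyses and may refer to them alone. Counting one comparison for each of the eight secondary objectives would also be wrong, because button use is examined in the PMPS arm only.
- **That the correction weakens detection of side-effects.** The Statistical plan names no test for side-effects.
- **That the Background voices a fear of under-sedation under PMPS.** The sentence "Under-sedation results in an anxious patient because their anxiolytic requirements are unmet during surgery" follows a statement about the difficulty of matching patients' preferences with ACPS. It describes the control regimen.
- **That superiority is claimed beyond propofol use.** Both the abstract's Discussion and the Statistical methods section tie superiority to propofol consumption.

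**Conclusion.** The concern holds as a mismatch between two secondary objectives and the analysis named for them. It is firm for anxiety, where the word used is equal, and softer for satisfaction. It does not depend on Bonferroni: at an assumed 0.5 SD deficit, 40–45% of trials with 36–40 per arm would give a non-significant result with no correction at all. The 65–77% figure is conditional on the correction covering these outcomes with 5 to 10 comparisons. If complete-case exclusions bring the number below 36 per arm, power is lower still. The primary hypothesis test and the sample size of 80 are not affected.

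**What to change.** 1. For anxiety and satisfaction, report the arm difference with an unadjusted 95% confidence interval, and state that a non-significant result is not evidence of equality.
2. Then choose one of two routes. Either reword both objectives as estimating the difference between arms, or claim not worse only if the interval excludes a margin fixed for that scale before the data are seen, and otherwise call the result inconclusive. The second route needs two margins, since the outcomes are on different scales.
3. State which comparisons the Bonferroni correction covers, and that these two objectives are not among them.

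The cost is wording and, on the second route, agreement on two margins. No more patients are needed. The downside is that the result may well be inconclusive: with an interval half-width of about 0.45–0.47 SD, of the margins tabulated only 0.8 SD could be met with good power. Rewording as estimation is the lighter choice and is sufficient.

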### Trial intervention

Propofol 1% is licensed in the UK for “Sedation for diagnostic and surgical procedures, alone or in combination with local or regional anaesthesia in adults and children > 1 month” [14]. The trial will be using propofol within the terms of this license. Patients randomised to PMPS will receive propofol according to the following algorithm: the effect-site target concentration of propofol will be commenced at 0.5 μg.mL^− 1^ and increased by 0.2 μg.mL^− 1^ (when the patient presses the button) to a maximum of 2.0 μg.mL^− 1^. Following a successful button-induced increase in the effect-site target, further button presses will not increase the target concentration for 2 min (this is termed the *lockout period*). If patients do not press the button for 15 min, the effect-site target will reduce by 0.1 μg.mL^− 1^, and will continue to reduce by 0.1 μg.mL^− 1^ every 15 min to a minimum of 0.5 μg.mL^− 1^ in the absence of a button-press. Patients randomised to ACPS will receive propofol according to the following algorithm: the effect-site concentration will be commenced at a level determined by the supervising clinical anaesthetist and incremented and decremented by them as they see fit. No maximum or baseline levels will be pre-specified. This constitutes standard clinical practice. Both groups will use Schnider effect-site TCI modelling.

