### Safety

All pre-existing medication taken by a participant as part of their usual medical care will be permitted. Co-administration of sedatives, hypnotics or analgesics during placement of spinal anaesthesia or during the intra-operative sedation regime at the discretion of the supervising clinical anaesthetist will be recorded. Behavioural disinhibition is a well-recognised side-effect of propofol sedation. This occurs regardless of whether the propofol is delivered by intermittent bolus, fixed rate infusion or target-controlled infusion. It manifests as patient movement (usually of the upper limbs) and/or talking. It does not always respond readily to simple verbal command from the supervising clinician to desist. The standard treatment for this is for the supervising clinical anaesthetist to actively alter the depth of sedation at their discretion by either lightening or deepening the degree of sedation according to clinical circumstances and their professional judgement. In either arm of the trial, if a patient displays disinhibited behaviour that is disruptive to surgery or potentially dangerous for the patient (for example, risking pulling out their intravenous cannula), the supervising clinical anaesthetist will be free to alter the patient’s depth of sedation either by lightening or deepening sedation, using a sedative agent of their discretion. This will be recorded. No medications will be specifically prohibited in this trial.

In order to detect physiological changes that may suggest unsafe sedation, both trial arms will have heart rate, respiratory rate, arterial oxygen saturations, blood pressure and depth of sedation measured and recorded at 5 min intervals throughout the sedation period. Adverse events, adverse device events, serious adverse events and serious adverse device events will be recorded and reported to the relevant bodies (trial Sponsor, device manufacturer, Research Ethics Committee, Medicine and Healthcare products Regulatory Agency).

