### Intervention

The usual clinical care of non-invasive physiological monitoring will be established by the supervising clinical anaesthetist. They will insert an intravenous cannula and spinal anaesthesia will be performed. When satisfied that adequate spinal anaesthesia has been accomplished, they will commence the participant on their allocated sedation regime.

Participants allocated to PMPS will have their sedation infusion commenced at the minimum level of 0.5 μg.mL^− 1^ and will be given the handheld trigger button to press. They will be told *“*Press the button if you want to be more sleepy*”*. Participants allocated to ACPS will be commenced on an effect-site-steered TCI propofol infusion. The supervising clinical anaesthetist will control the effect-site target at their discretion.

Both sedation regimes will commence in the anaesthetic room, prior to the participant moving to theatre. A study investigator will record physiological and sedation outcome measures at 5-min intervals throughout the sedation period.

The sedation regime will be discontinued at the end of surgery when skin clips are applied to the wound. This time will be noted by a study investigator. In the PMPS group the handheld button will be withdrawn from the patient and the TCI infusion stopped. In the ACPS group the TCI infusion will be stopped. If, for any reason, the sedation is discontinued prior to end of surgery, the reason will be noted in a free-text narrative response by a study investigator.

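### The airway side-effect is defined by the anaesthetist's manoeuvre and omits propofol reduction, so obstructions may be counted unevenly between ACPS and PMPS

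*Protocol article*

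**What the plan says.** The protocol article, under Study objectives, asks whether PMPS patients "experience a different incidence of airway, respiratory or cardiovascular sedation-related side-effects than patients who have undergone ACPS". It describes the airway component as "partial or complete airway obstruction that requires the usual clinical anaesthetist to apply one of the following interventions: chin-lift, jaw thrust, nasopharyngeal airway insertion", and the list ends with "oropharyngeal airway insertion, laryngeal mask insertion or endotracheal tube insertion". All six items are manual manoeuvres or airway devices. The respiratory component is built differently, on measured limits alone: "Respiratory sedation-related side-effects are respiratory rate fewer than 8 breaths per minute or arterial oxygen saturations less than 88" per cent in patients with COPD, or 94% in all others.

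Under Trial intervention, the ACPS target is "incremented and decremented by them as they see fit". For PMPS the only downward route described is automatic: "If patients do not press the button for 15 min, the effect-site target will reduce by 0.1" μg/mL, repeated every 15 minutes without a press, to a floor of 0.5 μg/mL.

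Two other places bear on control of depth in PMPS. Under Safety, when disinhibited behaviour in either arm disrupts surgery or endangers the patient, "the supervising clinical anaesthetist will be free to alter the patient’s depth of sedation either by lightening or deepening sedation", and this is recorded. Under Intervention, for both arms: "If, for any reason, the sedation is discontinued prior to end of surgery, the reason will be noted in a free-text narrative response".

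The Trial blinding section states that neither the supervising anaesthetist nor the investigator collecting intra-operative data is blinded.

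**The concern.** Whether an obstruction becomes an airway event depends on how an unblinded clinician treats it. One natural response, giving less propofol, is not on the list. An obstruction that clears when the target is lowered did not require a listed manoeuvre, so on a plain reading it is not an airway event.

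This would matter less if the unlisted response were equally available in both arms. As written, it is part of the ACPS regimen and absent from the PMPS algorithm. Control of the target is what is being randomised, so allocation could affect whether an obstruction is counted as well as whether it occurs.

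At stake is the airway part of one secondary objective. It still deserves care, because collecting safety data on the prototype device is a stated aim in the Abstract, and the results are meant to inform clinicians and device manufacturers.

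**Working it through.** **The plan's own figures.** The article gives no airway event rate and no calculation for this comparison, so there is no airway figure to reproduce. The only figure used here is the sample size. With means 1.580 (SD 0.755) and 2.231 (SD 0.915), 36 per arm gives 90.1% power by Welch's t test (35 per arm gives 89.2%), hence 72. Then 72 / 0.9 = 80, or 40 per arm. The stated figure reproduces and is not in question.

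**The passages side by side.**

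| Feature | ACPS | PMPS |
|---|---|---|
| Listed manoeuvre counts as an airway event | Yes | Yes |
| Propofol reduction alone counts as an airway event | Not listed | Not listed |
| Anaesthetist may lower the target during routine sedation | Yes, at discretion | Not described |
| Automatic reduction | None described | 0.1 μg/mL per 15 min without a press |
| Lightening for disinhibited behaviour | Yes, recorded | Yes, recorded |
| Early discontinuation, reason in free text | Yes | Yes |
| Respiratory limits counted whatever the treatment | Yes | Yes |

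The arms differ in the two rows on how the target can come down.

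**Illustration.** Let p be the true incidence of obstruction, assumed equal in both arms, and q the share relieved by propofol reduction alone and so not counted. Then:

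- counted events per arm = 40 × p × (1 − q)
- counted risk ratio, PMPS:ACPS = (1 − q in PMPS) / (1 − q in ACPS)

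The ratio does not depend on p. The values of p and q are assumptions. With p = 20% there are 40 × 0.20 = 8 true obstructions per arm:

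| q in ACPS | q in PMPS | Counted ACPS | Counted PMPS | Risk ratio |
|---|---|---|---|---|
| 50% | 50% | 4 | 4 | 1.0 |
| 50% | 25% | 4 | 6 | 1.5 |
| 25% | 0% | 6 | 8 | 1.33 |
| 50% | 0% | 4 | 8 | 2.0 |
| 75% | 0% | 2 | 8 | 4.0 |

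At p = 10% or 30% the counts scale and the ratios stay the same. If propofol reduction were used more often in PMPS than in ACPS, the ratio would fall below 1.

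**Masking is also possible.** PMPS is capped at 2.0 μg/mL and ACPS has no pre-specified maximum, so true incidence might be higher in ACPS. If it were 30% in ACPS and 15% in PMPS (12 and 6 of 40), with q = 50% in ACPS and 0% in PMPS, the counts would be 12 × 0.5 = 6 and 6, and the difference would disappear.

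**Would a spurious difference reach significance?** For 8 of 40 against 6, 4 or 2 of 40, Fisher's exact test gives p = 0.77, 0.35 and 0.09. The likelier harm is a misleading descriptive safety table, not a false positive test.

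**The case against.** The strongest reply has five parts.

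1. **The list may not be exclusive.** Airway side-effects are said to 'include' such obstructions, whereas respiratory ones 'are' the stated limits. This stands as a caution. The list is still the only counting rule given for airway events.

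2. **PMPS is not closed to the anaesthetist.** A reader might infer that the anaesthetist cannot lower or stop propofol in PMPS. The article does not say so. It allows lightening in either arm for disinhibition and foresees early discontinuation for any reason. On airway obstruction in PMPS it is silent, and the full clinical investigation plan, not shown, may cover it. This stands, and it is why the bias is possible and not established. What the two provisions do not supply is a record of a temporary target reduction made for an airway reason: one is tied to disinhibition, the other to discontinuation.

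3. **Early titration is part of ACPS.** If it averts a manoeuvre, the lower count is a real difference between regimens. That is fair for the question of which regimen needs more airway manoeuvres, and is a reason to keep that count. It does not answer how often obstruction occurs.

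4. **Other records exist.** Respiratory limits are counted whatever the treatment and recorded every 5 minutes in both arms, and adverse events and adverse device events are also recorded. Obstructions that cross a limit at a recording are caught, as respiratory events. Those relieved before then may not be.

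5. **An undercount needs substitution.** If the target is lowered and a manoeuvre is also used, the event is counted. This is correct, and the article gives no information on how often each happens.

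**Conclusion.** The concern holds in a limited form. The airway definition depends on an unblinded clinician's treatment response and leaves out propofol reduction. The written algorithms give the anaesthetist free downward control in ACPS and describe none in PMPS. Obstructions relieved by lowering propofol alone may therefore be missed more often in ACPS, which can bias the airway component of the seventh secondary objective.

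A reader might go further and infer that the definition does bias the comparison against PMPS. The article does not support that. Direction and size depend on the share managed by propofol reduction alone in each arm, which is unknown. With equal true incidence assumed, the counted risk ratio is 1.0 if the shares are equal, 1.5 at 50% against 25%, and 2.0 at 50% against 0%. The ratio of 4.0 needs 75% against none and is an extreme case.

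The respiratory and cardiovascular components and the primary outcome are not affected. This is a cheap improvement to a secondary outcome.

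**What to change.** Count as an airway event every partial or complete obstruction that the study investigator observes, in both arms and whatever the response. For each, record the response: a listed manoeuvre; propofol reduced, paused or stopped; or none. Report the count of obstructions requiring a listed manoeuvre as a second line, so that the need for airway intervention remains visible. The respiratory component is already defined without reference to treatment, so such a definition fits this trial.

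Reconcile Study objectives, Trial intervention, Safety and Intervention on what is recorded in each arm when propofol is reduced or stopped for an airway reason. This concerns recording only and sets no clinical rule.

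The cost is one extra field on the intra-operative form and a wording change. An investigator is already recording at 5-minute intervals throughout sedation. There are two downsides: some milder obstructions will be counted, and detection still rests on an unblinded observer, so the change removes dependence on the treatment response but not observer bias.
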